### Study design and population

2.1

TeleRiab4FRA is a randomized, controlled, prospective, monocentric, parallel-group, open-label, non-profit clinical trial designed to evaluate the effectiveness of a high-technology telerehabilitation program in frail and pre-frail older adults with chronic heart failure. The study compares an 8-week synchronous sensorimotor and cognitive telerehabilitation program with a caregiver-supervised home-based rehabilitation program matched for rehabilitation content and tailored according to the patient's frailty profile.

The trial will be conducted at the Cardiac Rehabilitation Unit of the AOU “San Giovanni di Dio e Ruggi d’Aragona”, Salerno, Italy. Eligible participants will be male and female patients aged 65 years or older, with a diagnosis of Chronic Heart Failure (CHF) for at least 6 months, clinically stable and receiving optimized pharmacological therapy for at least 1 month. Patients with HF with reduced, mildly reduced, or preserved ejection fraction will be eligible, provided that they are classified as New York Heart Association (NYHA) functional class I–III and present a condition of pre-frailty or frailty.

Frailty status will be documented using validated multidimensional and functional tools, including the Fried frailty phenotype (2), the Comprehensive Geriatric Assessment (CGA) (25), the Italian Frailty Index (IFI) (26), and the Short Physical Performance Battery (SPPB) (27). Patients will be considered eligible if they meet predefined criteria for pre-frailty or frailty according to at least one of these instruments. The presence of a caregiver will be required when necessary to support safe participation in the rehabilitation program and completion of home-based activities (Table 1).

**Table 1 T1:** Inclusion and exclusion criteria for the TeleRiab4FRA study. CGA, Comprehensive Geriatric Assessment; eGFR, estimated glomerular filtration rate; HFpEF, heart failure with preserved ejection fraction; HFmrEF, heart failure with mildly reduced ejection fraction; HFrEF, heart failure with reduced ejection fraction; IFI, Italian Frailty Index; NYHA, New York Heart Association; SPPB, Short Physical Performance Battery.

Inclusion criteria	Exclusion criteria
Age ≥ 65 years, male or female	Age < 65 years
Confirmed diagnosis of CHF for at least 6 months	NYHA class IV
Optimized and stable HF therapy for at least 1 month	Planned heart transplantation or ventricular assist device implantation within 6 months

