NYHA functional class I–III	Severe renal impairment, defined as eGFR < 30 mL/min/1.73 m^2^, or dialysis dependency
Any left ventricular ejection fraction phenotype: HFrEF, HFmrEF, or HFpEF	Severe comorbidities markedly limiting life expectancy
Pre-frailty or frailty documented by at least one validated tool: Fried phenotype, IFI Index, CGA, or SPPB	Absence of pre-frailty/frailty, defined as Fried = 0, IFI = 0, and SPPB ≥ 11/12, or SPPB = 10/12 without sit-to-stand impairment
Fried phenotype: pre-frailty = 1–2 criteria; frailty = ≥ 3 criteria	SPPB < 5/12, indicating severe functional impairment not compatible with safe protocol execution
IFI ≥ 1: pre-frailty = 1–16; moderate frailty = 16.1–27; severe frailty = 27.1–40	Inability to walk independently, even with walking aids
SPPB 5–9/12 compatible with functional frailty; SPPB 10/12 compatible with pre-frailty if impairment is attributable to sit-to-stand	Severe visual impairment preventing study procedures, even with caregiver support
Ability to provide informed consent or availability of a legally authorized representative	Current or suspected pregnancy
Presence of a caregiver, when required for safe participation	Inability or unwillingness to comply with study procedures

After screening and baseline assessment, participants will be randomized in a 1:1 ratio to either the telerehabilitation group or the control group. The telerehabilitation group will receive the rehabilitation program through a synchronous digital platform with remote monitoring of clinical parameters, while the control group will perform an individualized home-based program supervised by a caregiver or family member and supported by a daily activity diary. Both groups will receive motor and cognitive training tailored according to frailty status.

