Predefined exploratory subgroup analyses will examine whether treatment effects vary according to baseline frailty status (pre-frail versus frail, and where appropriate moderate versus severe frailty), NYHA functional class (I–II versus III), sex, and age (for example, ≤80 versus >80 years). Treatment-by-subgroup interaction terms may be estimated within the relevant ANCOVA or mixed-effects models. Because the trial is not powered for subgroup effects, these analyses will be considered hypothesis-generating and interpreted cautiously using interaction estimates and 95% confidence intervals.

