#### Sample size calculation

2.6.3

The sample size was calculated on the basis of the primary endpoint, defined as the change in functional capacity measured by VO₂peak during cardiopulmonary exercise testing from baseline to the end of the 8-week intervention.

A between-group difference of 2.5 mL/kg/min in VO₂peak (50) was considered clinically meaningful. Assuming a standard deviation of 3.5 mL/kg/min, corresponding to a Cohen's d effect size of approximately 0.71, the sample size calculation was performed using G*Power software, based on a two-tailed test for the difference between two independent means, with a significance level of *α* = 0.05, statistical power of 80%, and 1:1 allocation.

The calculation indicated that 33 participants per group, corresponding to 66 participants overall, are required to detect the expected difference in the primary endpoint. Considering an anticipated dropout rate of approximately 15%–20%, the study plans to enroll approximately 80 participants overall, in order to preserve adequate statistical power for the primary efficacy analysis.

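### The predefined age subgroup rests on a two-group cut offered only as an example; a continuous treatment-by-age interaction would use the data better, with the cut fixed for display

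*Protocol article*

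**What the plan says.** The last paragraph of 2.6.2 lists subgroup analyses by baseline frailty, NYHA class, sex and age, and calls them predefined and exploratory. Frailty is grouped as "pre-frail versus frail, and where appropriate moderate versus severe frailty". Age is grouped at a value given as an illustration: "sex, and age (for example, ≤80 versus >80 years".

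On method: "Treatment-by-subgroup interaction terms may be estimated within the relevant ANCOVA or mixed-effects models". On status: "Because the trial is not powered for subgroup effects, these analyses will be considered hypothesis-generating and interpreted cautiously". Interpretation is to rest on the interaction estimates and their 95% confidence intervals.

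Four other places bear on the point:

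- Table 1 (2.1) sets the age criterion, "Age ≥ 65 years, male or female", with no upper limit, and defines the frailty bands on the Italian Frailty Index (IFI): "pre-frailty = 1–16; moderate frailty = 16.1–27; severe frailty = 27.1–40".
- Section 2.1 stratifies randomisation by pre-frail/frail and by NYHA I–II/III. Age is not a stratification factor.
- Sections 2.2.1 and 2.2.2 set session frequency by pre-frail versus frail. Age plays no part.
- Section 2.6.1 names age as a possible ANCOVA covariate.

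**The concern.** A subgroup analysis is predefined only if its groups are. Here the age boundary is an example, so the text does not commit to it. The trial is open-label, and a boundary that can move makes the age result harder to trust, even as a hypothesis.

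The second issue is efficiency. Age is known in years for every participant. Splitting it at 80 treats a 66-year-old and a 79-year-old as alike and an 80-year-old and an 81-year-old as different. In a population that starts at 65, the upper group may also be small. The pre-frail/frail and NYHA groupings have a design reason because they are strata; the age cut has none that the article states.

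At stake is the precision of one exploratory estimate, namely whether the benefit of telerehabilitation changes with age. Nothing confirmatory depends on it.

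**Working it through.** **1. The plan's own figure.** Section 2.6.3 takes "A between-group difference of 2.5 mL/kg/min in VO₂peak (50) was considered clinically meaningful", an SD of 3.5, two-sided α of 0.05, 80% power and 1:1 allocation, and obtains 33 per group. A two-sample t-test calculation gives 31.8 per group at d = 2.5/3.5 and 32.1 at the rounded d = 0.71, hence 32 or 33. The stated 66 reproduces. With 80 enrolled and 15–20% dropout, 80 × 0.85 = 68 to 80 × 0.80 = 64 remain, so 66 analysed is a fair working number. The plan gives no figure for the age interaction.

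**2. Information kept by a cut.** If the treatment effect is linear in age, the share of interaction information kept by a two-group split is the squared correlation between age and the over-80 indicator. For normal age with a proportion p above the cut, this is φ(z)² / [p(1 − p)]. At p = 0.25, z = 0.674 and φ(z) = 0.318, so the share kept is 0.101 / 0.1875 = 0.54, a loss of 46%. The same formula gives a loss of 36% at p = 0.50, 51% at p = 0.20 and 66% at p = 0.10. None of this depends on the SD of VO₂peak.

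**3. Ages starting at 65.** The documents give no mean, SD or share over 80, so these distributions are assumptions: normal, truncated at 65, by simulation. Mean and SD are those before truncation.

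| Mean, SD | Share over 80 | Information kept | Loss |
|---|---|---|---|
| 73, 6 | 13% | 47% | 53% |
| 75, 6 | 21% | 55% | 45% |
| 77, 6 | 31% | 61% | 39% |
| 78, 7 | 40% | 65% | 35% |

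With 33 per arm, 13–40% over 80 means about 4 to 13 such patients per arm.

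Other shapes widen the range. Uniform ages give a loss of 25% (65–95), 28% (65–90) or 44% (65–85). A younger population loses more: 71% with mean 72 and SD 5, and 81% with mean 70 and SD 5, where only about 3% are over 80.

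**4. What this does to power.** Per SD of age, the standard error of a continuous interaction is 2 × 3.5 / √66 = 0.862 mL/kg/min. Under the cut, the expected z-value shrinks by the square root of the information kept. Two-sided 0.05 power, using the step 3 table:

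| Change in effect per SD of age (mL/kg/min) | Continuous age | Cut at 80 |
|---|---|---|
| 2.0 | 64% | 35–47% |
| 1.25 | 31% | 17–22% |
| 0.6 | 11% | 8–9% |

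The first row is an extreme case: a slope of 2.0 means the effect differs by 4.0 mL/kg/min between one SD below and one SD above the mean age, against a planned overall difference of 2.5.

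**5. Precision of the grouped estimate.** With 25% over 80 and 66 analysed, the standard error of the difference in effect between the age groups is 3.5 × √[4/(66 × 0.25) + 4/(66 × 0.75)] = 1.99 mL/kg/min. Power for a difference as large as 2.5 is about 24%, and about 30% even with an equal split.

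**The case against.** The strongest reply is that the section already limits these analyses. They are exploratory and declared unpowered, and interaction terms are only a possibility. Section 2.6 also refers to a separate statistical analysis plan, which is not shown and may fix the cut. This largely stands. It rules out saying that the trial tests age confirmatorily or that the boundary will be chosen after data are seen. What remains is that this text calls the analysis predefined, names two-group age as the method and leaves the boundary as an illustration.

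A reader might also infer that the moderate/severe frailty split adds to the loss. It does not: grouping frailty removes no information on the age interaction, and no loss on the frailty interaction has been calculated. Those bands are set in advance in Table 1 and the split is conditional. Session frequency also steps between IFI 16 and 16.1, so a straight line in IFI would smooth across a dosing boundary.

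A third reply is that the efficiency gain assumes linearity. That is correct. If the true effect modification were a step at exactly 80, the advantage would disappear and in fact reverse. The gain is also trivial when the slope is modest, as the last row in step 4 shows.

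**Conclusion.** The point holds as a minor improvement. The age boundary is not fixed in an analysis described as predefined, and grouping age at 80 is an inefficient way to examine a roughly linear change in effect. The loss is about 35–55% under the truncated-normal assumptions shown, and about 25% to 70% or more over wider ones.

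A reader might take 35–55% as a property of the trial. The documents do not support that, because they give no age distribution and the figure also rests on linearity. Nor does the point touch the primary comparison, its type I error or the sample size. Under either method, power for an age interaction stays below 80% at every slope examined, and it is low at modest slopes.

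**What to change.** In the subgroup paragraph of 2.6.2:

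- Estimate effect modification by age with a treatment-by-age interaction in the ANCOVA, with age in years, centred, and its main effect included.
- Report the estimated treatment effect with 95% CI at set ages, for example 70, 75, 80 and 85.
- Fix the ≤80/>80 split in advance by deleting the words that make it an example, and use it for display only.
- Keep pre-frail/frail, NYHA class and sex as categories. A continuous IFI interaction may be added as a supplement, with no claimed gain.

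The cost is wording only, since age is already collected. The downside is the linearity assumption. The grouped display lets readers see whether a threshold at 80 fits better.

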#### Sample size calculation

2.6.3

The sample size was calculated on the basis of the primary endpoint, defined as the change in functional capacity measured by VO₂peak during cardiopulmonary exercise testing from baseline to the end of the 8-week intervention.

A between-group difference of 2.5 mL/kg/min in VO₂peak (50) was considered clinically meaningful. Assuming a standard deviation of 3.5 mL/kg/min, corresponding to a Cohen's d effect size of approximately 0.71, the sample size calculation was performed using G*Power software, based on a two-tailed test for the difference between two independent means, with a significance level of *α* = 0.05, statistical power of 80%, and 1:1 allocation.

The calculation indicated that 33 participants per group, corresponding to 66 participants overall, are required to detect the expected difference in the primary endpoint. Considering an anticipated dropout rate of approximately 15%–20%, the study plans to enroll approximately 80 participants overall, in order to preserve adequate statistical power for the primary efficacy analysis.

#### Handling of missing data and dropouts

2.6.4

Missing data will be described by treatment group, outcome, and assessment timepoint. The amount, pattern, and potential reasons for missingness will be examined to evaluate whether missing data are likely to be missing completely at random, missing at random, or not missing at random.

The primary analysis will be conducted on the ITT population. Linear mixed models for repeated measures will be used as part of the analytical strategy because they allow inclusion of participants with partially observed follow-up data under the missing at random assumption. If the proportion of missing data at the primary post-treatment assessment is relevant or unbalanced between groups, sensitivity analyses using multiple imputation will be performed. The imputation model may include treatment group, baseline value of the outcome, age, sex, NYHA class, frailty level, and other variables associated with missingness or outcome values.

Dropouts and protocol deviations will be documented in the CRF, including the timing and reason for withdrawal whenever available. Participants who discontinue the intervention but remain available for outcome assessment will be invited to complete follow-up evaluations according to the original study schedule. Per-protocol analyses will be conducted as sensitivity analyses to assess the robustness of the primary findings among participants with adequate intervention exposure and without major protocol deviations.

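### The only sensitivity analysis named for missing week-8 VO₂peak appears to share the missing-at-random assumption it should test

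*Protocol article*

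**What the plan says.** Section 2.6.4 (Handling of missing data and dropouts) does four things.

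- It will examine the amount, pattern and possible reasons for missingness, to judge whether data are likely to be "missing completely at random, missing at random, or not missing at random".
- It supports the linear mixed model because that model permits "inclusion of participants with partially observed follow-up data under the missing at random assumption".
- If missingness at the primary visit is big enough to matter or differs between arms, "sensitivity analyses using multiple imputation will be performed". The imputation model may use treatment group, baseline value, age, sex, NYHA class, frailty level, and other variables related to missingness or to the outcome.
- Participants who stop the programme but can still be assessed are invited to the scheduled visits, and reasons for withdrawal are recorded where available.

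The other sensitivity analysis is per-protocol: at least 80% of sessions and no major deviation (section 2.6). The primary analysis is an ANCOVA of week-8 VO₂peak adjusted for baseline (2.6.1), declared as intention-to-treat in all randomised participants (2.6). Section 2.6.3 plans about 80 participants, expecting 15–20% dropout.

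**The concern.** A sensitivity analysis for missing data should change the assumption that cannot be verified and show whether the conclusion moves. Section 2.6.4 names the possibility that data are not missing at random (MNAR) but attaches no analysis to it. Observed data cannot separate MAR from MNAR, so a review of patterns and reasons cannot close the question.

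As described, the imputation predicts a missing week-8 value from observed variables, including arm. Without a shift or a reference-arm step, this is the standard MAR form: dropouts receive the outcomes of comparable participants in their own arm who were measured. The per-protocol analysis imputes nothing and selects adherent participants, so it is silent on unobserved outcomes.

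MAR is open to doubt here. In frail older adults with heart failure, decompensation or intolerance may cause a missed exercise test and also lower VO₂peak. The Limitations section says retention may depend on digital literacy, connectivity and caregiver availability, none of which is named in the imputation model. Table 4 has no week-4 VO₂peak, so a participant lost before week 8 and not seen again has only a baseline value, and the mixed model recovers little about that person. If ANCOVA, mixed model and imputation then agree, readers may take this as robustness when one assumption has been applied three times.

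**Working it through.** **Inputs from section 2.6.3.** "A between-group difference of 2.5 mL/kg/min in VO₂peak"; SD 3.5; calculation "based on a two-tailed test for the difference between two independent means"; two-sided α 0.05; "statistical power of 80%, and 1:1 allocation"; about 80 enrolled (40 per arm); dropout 15–20%.

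**The plan's own figure.** d = 2.5/3.5 = 0.714. With the noncentral t distribution, d rounded to 0.71 needs 33 per group and unrounded d needs 32. The stated 33 is reproduced; power at 33 per group is 81.1% to 81.5%.

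**Scenario (assumed, not in the documents).** Equal dropout proportion p in both arms; every dropout unmeasured at week 8; telerehabilitation dropouts end at the control mean.

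All-randomised effect = 2.5 × (1 − p). SE = 3.5 × √(2/n), with n = 40 × (1 − p) measured per arm.

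| Dropout | n per arm | SE | All-randomised effect | MAR methods return | Power for 2.5 | Power for the all-randomised effect |
|---|---|---|---|---|---|---|
| 15% | 34 | 0.849 | 2.125 | about 2.5 | 82.7% | 69.4% |
| 20% | 32 | 0.875 | 2.0 | about 2.5 | 80.3% | 61.4% |

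A simulation of this scenario (1,000 trials, 20 imputations, assumed baseline to week-8 correlation 0.6) gave 2.49 for the observed-case ANCOVA and 2.49 for MAR imputation at both dropout rates. The all-randomised values were 2.12 and 1.99. Imputing telerehabilitation dropouts from the control model returned 2.12 and 1.99. The two MAR methods agreed with each other and both missed the target.

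**Effect on the conclusion.** Same SE, t with 2n − 2 degrees of freedom, approximate.

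| Dropout | Observed difference (p) | Telerehabilitation dropouts at control mean (p) | Downward shift in telerehabilitation dropouts at which the 95% CI reaches 0 |
|---|---|---|---|
| 15% | 2.5 (0.004) | 2.125 (0.015) | (2.5 − 1.695)/0.15 = 5.4 |
| 20% | 2.5 (0.006) | 2.0 (0.026) | (2.5 − 1.749)/0.20 = 3.75 |
| 15% | 2.0 (0.021) | 1.7 (0.049) | (2.0 − 1.695)/0.15 = 2.0 |
| 20% | 2.0 (0.026) | 1.6 (0.072) | (2.0 − 1.749)/0.20 = 1.25 |

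Here 1.695 and 1.749 are the smallest significant differences (critical t × SE).

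**If half the dropouts are measured (assumed).** At 20%, 32 completers and 4 measured dropouts per arm give 2.5 × 32/36 = 2.22 against 2.0, a bias of 0.22. At 15%, 2.5 × 34/37 = 2.30 against 2.125, a bias of 0.17.

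**Direction.** With downward shifts δT and δC in the two arms and equal dropout, estimate = observed − p × (δT − δC). If control dropouts end 2.5 below their MAR prediction and telerehabilitation dropouts do not, then at 20% dropout 2.5 becomes 3.0, and the MAR estimate was too small.

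**Baseline adjustment.** The SEs above ignore it. If 3.5 is the SD of the week-8 value and the correlation is 0.6, SE at 20% is 0.875 × √(1 − 0.36) = 0.70, and 1.6 has p ≈ 0.026 rather than 0.072. The documents do not say which SD the 3.5 is.

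**The case against.** The strongest reply is that this article condenses a fuller plan. Section 2.6 refers to a statistical analysis plan that is not shown, and delta adjustment is the kind of detail such a plan holds. The article also does not label the imputation as MAR. Multiple imputation can carry MNAR scenarios, and the model may include variables related to the outcome; week-4 frailty, SPPB, adherence and adverse events could absorb part of the signal. This stands as a limit on certainty: the MAR reading is inferred from the model described. It does not remove the point, because section 2.6.4 is not silent. It raises MNAR, names one method as the sensitivity analysis, makes it conditional, and describes it without any departure from MAR.

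Second, inviting discontinuers to assessments is a real safeguard. Those who attend contribute measured values, so the 0.375 to 0.5 mL/kg/min bias is an upper range for this scenario.

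Third, a reader might infer that the plan is biased in favour of telerehabilitation. The documents do not support one direction. Control participants exercise without real-time professional supervision, and if their dropouts fare worse the bias reverses.

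Fourth, a reader might infer that a positive result would be overturned. An observed 2.5 survives the scenario at both dropout rates, and at 20% tipping needs a shift of about 3.75, which is 1.5 times the assumed effect.

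Finally, reviewing withdrawal reasons to judge what is plausible is legitimate. Only the idea that the data could settle the mechanism would be wrong.

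**Conclusion.** The point holds in a limited form. As described, the planned imputation shares the assumption of the mixed model and of an ANCOVA on observed cases, the per-protocol analysis does not fill the gap, and agreement among them would not show robustness to MNAR.

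The illustrated overstatement is 0.375 to 0.5 mL/kg/min, or 15–20% of the assumed effect. It rests on equal dropout, no dropout being measured, and telerehabilitation dropouts ending at the control mean. It is smaller if discontinuers attend and may reverse if control dropouts do worse. A difference near 2.5 would stand. A difference near 2.0 would be borderline at 15% dropout (p ≈ 0.049) and lost at 20% (p ≈ 0.07) on the unadjusted SE, though strong baseline adjustment could keep it significant. The plan as written could not tell readers which case applies. It should be changed, but it does not invalidate the primary analysis.

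**What to change.** In section 2.6.4, and in the statistical analysis plan if it does not already do so:

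1. Prespecify a delta-adjusted tipping-point multiple imputation of week-8 VO₂peak, run whatever the amount or balance of missing data. Vary the shift separately in each arm, and report the shift, or pair of shifts, at which the 95% CI for the adjusted difference first includes 0.
2. Control-based imputation of telerehabilitation dropouts may be added as one labelled scenario. Because the control is an active, content-matched programme, it credits dropouts with that programme's outcome and does not represent loss of all rehabilitation benefit.
3. State that the imputation without a shift assumes MAR, and present it as the starting point of the tipping-point analysis.
4. Keep the review of withdrawal reasons and use it to judge which shifts are plausible. Add that observed data cannot separate MAR from MNAR.

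The cost is wording and a little more analysis work, with no new data or patients. The sensitivity estimates may be less favourable than the MAR ones.
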